**Trial status:**

Enrolment began in January 2017 and follow-up is estimated to be completed by April 2019. As of 1 February 2019, 742 children are still contributing data to the ZTDT study.

What is already known on this topic?Therapeutic zinc supplementation has been recommended by WHO/Unicef for standard diarrhoea case management since 2004.Research evidence had shown zinc reduced the duration and severity of the acute diarrhoea, and lowered the risk of persistent diarrhoea.However, many trials noted that current dosage (20 mg/day for children aged >6 months) is associated with vomiting and possibly poor compliance.

What this study hopes to add?This study evaluates whether lower doses of zinc (10 mg/5 mg) are non-inferior to the standard dose in efficacy but superior for vomiting.If vomiting is less frequent and efficacy is maintained with low-dose zinc, caregiver acceptability may improve, leading to greater utilisation and better health outcomes.

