3summarised the findings for acute and persistent diarrhoea from a total of 22 zinc intervention trials, using a range of zinc dosing (5–45 mg/day). In 11 acute diarrhoea trials (n=4438), the proportion of participants who vomited after the initial dose was significantly higher with zinc use than with placebo (12.7% vs 7.6%; relative risk [RR]: 1.55; 95% CI: 1.30 to 1.84; p≤0.001). According to the review by Lazzerini and Wanzira,^7^ the risk of vomiting increased with zinc supplementation in both children older than age 6 months (risk ratio 1.57, 95% CI 1.32 to 1.86; 2605 children, 6 trials) as well as children younger than 6 months of age (risk ratio 1.54, 95% CI 1.05 to 2.24; 1334 children, 2 trials). Other studies have also reported that therapeutic zinc supplementation during diarrhoea causes higher rates of vomiting.^10–12^

Thus, although substantial evidence supports the efficacy of zinc supplementation during episodes of diarrhoea, vomiting is significantly more common among supplemented children. Lower doses of zinc, provided they are equally effective, might have the advantage of reducing side effects, increasing compliance and programmatic roll-out. If the zinc dose for diarrhoea treatment and zinc deficiency can be uniform, then the national essential drug lists can be simplified. Therefore, there exists an important rationale to identify the dose of zinc supplementation associated with both efficacy and an improved safety profile. We present the protocol for a two-centre, randomised, double-blind controlled trial of three doses of zinc conducted in Tanzania and India. The overall goals of the study are to evaluate the non-inferiority, safety and acceptability of the two lower zinc doses (5 and 10 mg/day) versus standard zinc dose (20 mg/day).

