### Primary and secondary objectives

The overall aim of ZTDT is to identify the optimal dose of zinc in children under 5 years with acute diarrhoea.

The primary aims of the study are: (1) to assess whether lower doses of zinc (5 or 10 mg/day) are at least as effective as the standard dose of zinc (20 mg/day) in children aged 6–59 months, in terms of burden of illness (percentage of subjects with diarrhoea lasting >5 days; mean number of loose or watery stools during follow-up) and (2) to evaluate the improved effectiveness by reduction in the risk of vomiting in 30 min after receipt of the supplement in low-dose supplemental zinc (5 or 10 mg/day) in comparison to standard dose of zinc (20 mg/day).

Secondary aims of the study are: (1) to explore whether lower doses of zinc have any impact on postacute illness morbidity outcomes assessed at 30, 45 and 60 days, (2) to explore whether duration of treatment, estimated by mother’s reports and collection of used zinc blister packs, has any impact on the primary outcomes, (3) to determine the acceptability of low-dose supplemental zinc compared with standard zinc dose based on an acceptability scale and (4) to determine whether the different doses of zinc are associated with differential plasma zinc levels at days 3, 7, 15, 21 and 30 after randomisation.

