### Interventions

Children are randomised to receive one of the three zinc sulfate regimens (each taken once daily for 14 days): (1) 5 mg; (2) 10 mg or (3) 20 mg. The zinc tablet (all three regimens) ingredients include aerosil, maize starch, ethylvanillin (a vanilla flavour), aspartame, magnesium stearate vegetal and vivapur. The three study tablets have identical appearance, taste and smell. The supplement is a dispersible tablet that dissolves in water or breast milk in about 20 s. The caretakers are instructed to dissolve the tablet in 5–10 mL of water or breast milk immediately before administration. Children receive zinc supplementation for 14 days. The first dose of study drug is given at the health facility in which the child is enrolled.

All three doses of the regimen are packaged identically; 10 tablets in 1 blister, 2 blisters in 1 pack (extra doses are provided for redosing in case of vomiting). Each pack is prelabelled with participant ID. Study regimen is manufactured by Laboratoires Pharmaceutiques Rodael, France and shipped to WHO for randomisation and labelling, before shipment to recruitment sites (as described in ’Randomisation, allocation, concealment and masking' section).

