### Adherence assessment

Adherence to the study regimen is optimised by close follow-up: either in person (clinic/home visits) or telephone contact on days 3, 5, 7, 10 and 15. Adherence to the regimen is measured by counting the numbers of unused tablets during each follow-up visit. Study workers/research assistants physically count the tablets during home or clinic visits. We give the mother/caregiver a small booklet to record every successful administration as well as any failed attempts to administer the intervention. Study worker reviews the diary card on each visit and collects filled diary card on day 15 visit.

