### Sensitivity analyses and modification of treatment effect

Although randomisation is designed such that, on average, treatment groups will be balanced with respect to all baseline prognostic factors, this may not be true in all cases. As a result, we will re-assess treatment effects as observed in the original analysis after adjusting for factors that are potentially imbalanced across randomised arms. If imbalance occurs, we will compare and present the results for both unadjusted and adjusted analyses.

In addition, the study was not designed to detect effect modification of the treatment effect among subgroups of children. As a result, we acknowledge that we are likely underpowered to detect differences in the magnitude of a treatment effect among subgroups unless there is strong effect modification. The potential baseline effect modifiers we plan to explore include: study site (India/Tanzania), child age (<12 vs >12 months), child sex (male vs female), prior receipt of rotavirus vaccine (yes vs no), maternal HIV status (yes vs no), dysentery at enrolment (yes vs no), baseline dehydration status (yes vs no), baseline axillary temperature (<38°C vs >38°C), baseline respiratory rate, recent antibiotic use (yes vs no), intercurrent illness (cough, difficulty breathing or earache), current breastfeeding status (yes vs no) and prior breastfeeding status (yes vs no). Additional variables that we will test for effect modification will include child anthropometric measures (length/height for age, weight for age and weight for length/height z-scores and MUAC), family socioeconomic status (<median wealth index, >median wealth index), maternal education, household water quality (improved vs unimproved), household sanitation quality (improved vs unimproved), baseline plasma zinc levels (<median, >median) and trial regimen adherence (<median, >median). Factor analysis will be used to derive wealth index from family possession variables. WHO/Unicef Joint Monitoring Programme definitions will be used to clarify improved versus unimproved for the household water quality and sanitation.^16^

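### Regimen adherence as an effect modifier and treatment duration as an exposure are both measured after randomisation; if recovery also drives them, they can show false dose or duration effects

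*Protocol article*

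**What the plan says.** Under Sensitivity analyses and modification of treatment effect, a list of baseline factors is followed by a second list, introduced by "Additional variables that we will test for effect modification will include". That second list includes "trial regimen adherence (<median, >median").

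Under Primary and secondary objectives, secondary aim 2 is to "explore whether duration of treatment, estimated by mother’s reports and collection of used zinc blister packs, has any impact on the primary outcomes".

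Other sections fix the timing and the expected direction:

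- Interventions: "Children receive zinc supplementation for 14 days". The pack also holds spare tablets for redosing after vomiting.
- Adherence assessment: "Adherence to the regimen is measured by counting the numbers of unused tablets during each follow-up visit".
- Key-message box under Trial status: the current dose "is associated with vomiting and possibly poor compliance".
- Background: lower doses "might have the advantage of reducing side effects, increasing compliance and programmatic roll-out".
- Outcome measures: adherence is a secondary outcome and appears twice in the list (items iv and viii).
- Statistical analysis: the per-protocol set is defined on zinc taken in the first 5 days, and the reason given is that the primary outcome is diarrhoea beyond 5 days. Neither the adherence subgroup nor aim 2 carries that limit.

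**The concern.** A subgroup factor keeps the randomised comparison intact only if treatment cannot have changed it. Adherence over 14 days is not such a factor. The trial's own rationale is that dose changes vomiting and vomiting changes compliance, and adherence is also to be analysed as an outcome of dose. Unused-tablet counts further reflect redosing after vomiting, and vomiting is itself a primary outcome.

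Aim 2 has a timing problem as well. Whether diarrhoea lasts beyond 5 days is known well before the 14-day course ends, so much of the duration measure accrues after the outcome. A caregiver may stop zinc because the child is well, or continue because the child is still ill. The association then runs from outcome to exposure.

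At stake is the reading of two exploratory results: a dose effect that seems confined to good or poor adherers, and an apparent harm of longer treatment. The Discussion expects the findings to feed into revision of the WHO diarrhoea guidelines, so a misreading would matter.

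**Working it through.** The article gives no figure for either analysis, so there is nothing to reproduce. The checks below ask what each analysis shows when the truth is no effect.

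**Timing.** Duration runs from randomisation to the last diarrhoea day before two diarrhoea-free days. A child whose last diarrhoea day is day 5 is classified once days 6 and 7 are free. The outcome is therefore decided by about day 5 to 7, which leaves 14 − 7 = 7 to 14 − 5 = 9 treatment days after it.

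**Aim 2, crude completer contrast.**

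Inputs: 16% with diarrhoea beyond 5 days (Table 1). Completion is assumed at 90% if still ill, and at a fraction c if recovered.

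- Risk in completers = 0.16×0.9 / (0.16×0.9 + 0.84×c)
- Risk in non-completers = 0.16×0.1 / (0.16×0.1 + 0.84×(1−c))

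| c | Completers | Non-completers | False risk ratio |
|---|---|---|---|
| 0.70 | 0.144/0.732 = 19.7% | 0.016/0.268 = 6.0% | 3.3 |
| 0.80 | 0.144/0.816 = 17.6% | 0.016/0.184 = 8.7% | 2.0 |
| 0.85 | 0.144/0.858 = 16.8% | 0.016/0.142 = 11.3% | 1.5 |
| 0.90 | 16.0% | 16.0% | 1.0 |

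The bias disappears only when completion does not depend on recovery.

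**Adherence subgroup.**

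Take one lower-dose arm and the 20 mg arm, each with 16% prolonged and no effect of dose or adherence on outcome. Let latent adherence be normal with SD 1 and mean μ(d,y), where d is the arm and y = 1 if prolonged, and split at the pooled median m. Then

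Risk in the low half of arm d = 0.16Φ(m−μ(d,1)) / [0.16Φ(m−μ(d,1)) + 0.84Φ(m−μ(d,0))],

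and the high half uses 1−Φ in place of Φ. If adherence does not depend on recovery, μ(d,1) = μ(d,0), the Φ terms cancel, and every cell is 16% whatever the dose shift.

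Worked case: 20 mg lowers adherence by 0.3 SD and still being ill raises it by 0.5 SD, so m ≈ −0.07.

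- Low half, lower dose: 0.16Φ(−0.57) / [0.16Φ(−0.57) + 0.84Φ(−0.07)] ≈ 10.3%
- Low half, 20 mg: 0.16Φ(−0.27) / [0.16Φ(−0.27) + 0.84Φ(0.23)] ≈ 11.3%
- False difference: −1.0 point

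In the table, differences are lower dose minus 20 mg, in percentage points. The shifts are assumptions.

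| Dose shift | Recovery shift | Low half | High half | Risk ratio, high v low adherence |
|---|---|---|---|---|
| 0.3 | 0 | 0.0 | 0.0 | 1.0 |
| 0 | 0.5 | 0.0 | 0.0 | 2.0 |
| 0.1 | 0.25 | −0.2 | −0.2 | 1.4 |
| 0.3 | 0.5 | −1.0 | −1.5 | 2.0 |
| 0.5 | 1.0 | −2.1 | −5.3 | 3.9 |
| recovered children on 20 mg stop a further 0.3 SD earlier | 0.25 | +2.4 | −4.1 | 1.7 |

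A simulation of 400,000 children per arm gave the same pattern. For scale, the non-inferiority margin for this outcome is 4 points.

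**The case against.** The case on the other side has real force on several points.

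- A reader might infer that the dose–compliance link is enough to bias the adherence subgroup. It is not: with no link between adherence and recovery or prognosis, the bias is zero (first row of the table). The article states only the dose link. Stopping on recovery is plausible but is an inference, so the results could be biased; it does not follow that they would be.
- A reader might try to size the subgroup bias through vomiting, for example 20% v 15% vomiting with risks of 25% in vomiters and 14% in others. That is not a null case. The whole arms already differ: 0.20×0.25 + 0.80×0.14 = 16.20% against 0.15×0.25 + 0.85×0.14 = 15.65%, a gap of 0.55 points before any split.
- A reader might infer that aim 2 prescribes the completer contrast shown here. It states no model or exposure window, and such detail may sit in an analysis plan that is not shown. The risk ratios show what a crude version would give. The aim itself still relates duration to outcomes that largely precede it.
- Aim 2 covers all the primary outcomes. Vomiting is recorded after each dose for 14 days, so the timing argument does not carry over to it unchanged.
- A reader might infer that the article calls adherence a baseline factor, or that the main conclusions are at risk. Adherence sits in the separate second list. The primary analyses are intention-to-treat and use neither variable. Aim 2 is worded as exploration, and the subgroup section warns of low power.

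What remains is that the article fixes the variable, the cut-point and its use as a modifier. Its caution there concerns power, and nothing says that these are not randomised comparisons.

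**Conclusion.** The point holds as a fault in two exploratory analyses. Both use a variable that arises after randomisation, that the article expects dose to change and, for diarrhoea beyond 5 days, that is largely recorded after the outcome is decided. The per-protocol definition recognises this timing, but neither of these analyses does.

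The size rests on assumptions that the article does not supply. For aim 2, completion of 90% if still ill against 70–80% if recovered gives a false risk ratio of 3.3 to 2.0, and 85% gives 1.5. For the adherence subgroup, false dose differences run from nil, if adherence depends on only one of dose and recovery, through about 0.2 points with weak links, to the order of the 4-point margin with strong or interacting links.

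The documents do not support a claim that bias is certain, nor that the intention-to-treat non-inferiority and superiority conclusions are affected. The change should be made, but the trial's main result does not depend on it.

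**What to change.** 1. Remove regimen adherence from the list of effect modifiers. Report it by arm as the secondary outcome it already is.
2. For aim 2 and diarrhoea beyond 5 days, count only zinc taken before the outcome is settled, in line with the first-5-days window of the per-protocol definition. Do not use later treatment days as exposure for this outcome.
3. Label the aim 2 result observational and not a randomised comparison. The label is needed even with the shorter window, because a child who recovers on day 2 may stop zinc on day 3.

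A landmark analysis of children still ill on a given day, adjusted for vomiting, is not a clean alternative. It conditions on states that dose may itself have changed.

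The cost is wording only, with no new data. One exploratory subgroup is lost, and the exposure range for aim 2 is narrower.

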### Monitoring

#### Data and Safety Monitoring Board

A Data Safety and Monitoring Board (DSMB) has been established to monitor SAEs and to review the statistical analysis plan and associated stopping rules for benefit, futility or harm determined using O’Brien-Fleming stopping boundaries. The DSMB includes five members with expertise in clinical trials, statistics, child mortality assessment, paediatric care in resource-limited settings or practical experience from each study country. The DSMB meets electronically or in person at least every 6 months. SAEs related to study participation are monitored in real-time, are summarised and reported to study investigators, WHO and relevant institutional review boards (IRBs) within 24 hours of notification in India and 72 hours of notification in Tanzania. Both sites are required to report to WHO within 72 hours of notification. Frequencies and descriptions of SAEs are pooled each month by the data management team at WHO and circulated to investigators, DSMB and IRBs. When more than half of the person-time is accrued in the study, the DSMB will review an interim data analysis by arm to determine whether stopping boundaries have been crossed.

#### Auditing

The sites are responsible for internal quality checks. WHO coordinators conduct at least one or two site monitoring visits per year to each site.

## Discussion

Zinc supplementation in children during episodes of diarrhoea results in several advantages as described earlier.^1 7 12^ Dose recommendations from WHO/Unicef were primarily based on previous clinical studies of zinc treatment of diarrhoea that used these amounts of zinc. Moreover, because zinc is absorbed less efficiently during diarrhoea,^17^ it has been assumed that the therapeutic dose for treatment of diarrhoea should be substantially greater than the RDA for zinc (3–5 mg/day for children aged <5 years), depending on bioavailability from the usual diet.^9^ Therefore, ZTDT was designed to examine the optimal therapeutic dose of zinc supplementation for children aged under 5 with acute diarrhoea in a south Asian country and a sub-Saharan African country.

A recent search of clinicaltrials.gov found no other clinical trials that are determining an optimal zinc therapeutic dose for children with acute diarrhoea. An additional search on PubMed, Google Scholar and other search engines was carried out where it was noted that one study was found to determine the optimal dose of zinc supplementation in diarrhoea.^18^ The double-blind randomised trial was carried out using 10 or 20 mg zinc sulfate versus placebo. No difference in duration nor frequency of diarrhoea was noted. However, this study was carried out in Switzerland, where the epidemiology of acute childhood diarrhoea is different than in India or Tanzania. As a result, ZTDT will likely be the first randomised trial in low-resource settings to determine the optimal dose of therapeutic zinc in children with acute diarrhoea.

Overall, the ZTDT study will measure important clinical outcomes (outcome of diarrhoea on growth, frequency of vomiting) in a large number of children under 5 years being treated for acute diarrhoea in India and Tanzania. It will also provide evidence for the effect of zinc on plasma zinc concentrations over several days after supplementation, the effect of zinc on postillness outcomes as well as the acceptability of zinc supplementation. The trial results will be communicated in academic journals and at the national and local levels in Tanzania and India through policy briefs and dissemination meetings. The results of ZTDT will likely be generalisable to children under 5 years with acute diarrhoea in similar resource-limited settings and as such will have global relevance. The findings will be an important consideration in any further revision of the WHO technical guidelines on diarrhoea case management.

10.1136/bmjpo-2019-000460.supp4Supplementary file 4

10.1136/bmjpo-2019-000460.supp5Supplementary file 5
